## Abstract

**Background:**

Nutrition is able to alter the cardiovascular health of the general population. However, the optimal dietary strategy for cardiovascular disease prevention is still far from being defined. Mediterranean and vegetarian diets are those reporting the greatest grade of evidence in the literature, but no experimental studies comparing these two dietary patterns are available.

**Methods/design:**

This is an open randomized crossover clinical trial including healthy subjects with a low-to-medium cardiovascular risk profile, characterized by being overweight and by the presence of at least an additional metabolic risk factor (abdominal obesity, high total cholesterol, high LDL cholesterol, high triglycerides, impaired glucose fasting levels) but free from medications. A total of 100 subjects will be included and randomly assigned to two groups: Mediterranean calorie-restricted diet (*n* = 50) and vegetarian calorie-restricted diet (*n* = 50). The intervention phases will last 3 months each, and at the end of intervention phase I the groups will be crossed over. The two diets will be isocaloric and of three different sizes (1400 – 1600 – 1800 kcal/day), according to specific energy requirements. Adherence to the dietary intervention will be established through questionnaires and 24-h dietary recall. Anthropometric measurements, body composition, blood samples and stool samples will be obtained from each participant at the beginning and at the end of each intervention phase. The primary outcome measure will be change in weight from baseline. The secondary outcome measures will be variations of anthropometric and bioelectrical impedance variables as well as traditional and innovative cardiovascular biomarkers.

**Discussion:**

Despite all the data supporting the efficacy of Mediterranean and vegetarian diets on the prevention of cardiovascular diseases, no studies have directly compared these two dietary profiles. The trial will test whether there are statistically significant differences between these dietary profiles in reducing the cardiovascular risk burden for the general population.

**Trial registration:**

ClinicalTrials.gov NCT02641834

**Electronic supplementary material:**

The online version of this article (doi:10.1186/s13063-016-1353-x) contains supplementary material, which is available to authorized users.

## Background

Nutrition is able to substantially alter the health status of the general population [1]. In industrialized countries the most important association between diet and health is the relationship with cardiovascular disease, the leading cause of death and disability worldwide. Therefore, the ability to identify with certainty the relationship between diet and cardiovascular disease appears to be a key element in the implementation of specific primary prevention strategies [2]. Recent studies have focussed their interest on the impact of a whole dietary approach rather than on isolating single nutrients on the occurrence of cardiovascular disease; it is recognized that analyses of single nutrients ignore the important and complex interactions between components of a diet and, more importantly, ignore the fact that people do not eat isolated nutrients [3, 4]. However, an optimal dietary strategy for the prevention of cardiovascular disease has not been found [5].

Several models of diet have been imposed on public attention, but those that have received the most interest are the Mediterranean and vegetarian diets [6, 7]. These dietary patterns seem to exert protective effects on blood pressure, lipid profiles, cardiovascular diseases and metabolic parameters.

The term Mediterranean diet has been widely used to describe the traditional dietary habits of people in Crete, South Italy and other Mediterranean countries during the decade of the 1960s. This dietary pattern is characterized by plentiful plant-derived foods (fruits, vegetables, breads, other forms of cereals, beans, nuts and seeds), olive oil as the principal source of fat, moderate amounts of dairy products (mainly cheese and yogurt), low-to-moderate amounts of fish and meat and a moderate consumption, usually with meals. Since the results of the first data from the Seven Countries Study, several studies in different populations have established a beneficial role for the main components of the Mediterranean diet on the occurrence of cardiovascular and chronic degenerative diseases [8]. Recently, a meta-analysis conducted by our group has revealed, in a population of more than 2 million people, that a strict adherence to a Mediterranean dietary pattern is associated with a significant improvement in health status, as seen by a significant reduction in overall mortality (10 %) and incidence of and/or mortality from cardiovascular diseases (9 %) [9].

A vegetarian diet is a dietary profile characterized by abstention from consuming meat and meat products, poultry, seafood and flesh from any other animal. In the past few decades, some case-control and cohort prospective studies reported beneficial effects of this dietary profile on the occurrence of cardiovascular and neoplastic disease. Very recently, our group conducted a systematic review with a meta-analysis on more than 120,000 vegetarians, showing that adherence to a vegetarian dietary pattern helps to determine, among case-control studies, lower levels of the most important risk factor for chronic disease, along with a reduced risk of occurrence for ischemic heart disease (–25 %) when cohort prospective studies were taken into account [10].

Despite all these findings, however, to the best of our knowledge, no randomized controlled trial that compares, in the same group of patients, the efficacy of nutritional interventions based on Mediterranean and vegetarian dietary patterns is available in the literature. To date, it is unclear whether the supposed health benefits for vegetarians can be attributed to the absence of meat in the diet, to the increased consumption of particular food component(s), to the pattern of foods eaten within the vegetarian diet or to other healthy lifestyle components often associated with vegetarianism.

Hence, we aimed to design this randomized, open, crossover clinical trial that will test whether there is a difference between a vegetarian calorie-restricted diet and a Mediterranean calorie-restricted diet in reducing total weight and ameliorating the cardiovascular risk profile of a clinically healthy group of subjects.

## Methods/design

### Study design and setting

The randomized, open, crossover clinical trial will be conducted at the Unit of Clinical Nutrition of the Careggi University Hospital, Florence, Italy. A crossover design will be implemented to allow comparison of the vegetarian and Mediterranean diets within the same individual. Participants will act as their own controls in crossover studies, so individual differences will be controlled for, making the error variance smaller and subsequently reducing the sample size required to find a significant effect due to increased statistical power. This design will also be adopted in an effort to minimize attrition and to maximize participant interest and compliance by enabling each participant to experience both diet conditions. The study design follows the SPIRIT guidelines (see Additional files 1 and 2).

### Eligibility criteria

Eligible participants will be clinically healthy subjects (aged 18–75 years) with a low-to-medium cardiovascular risk profile (1–5 % according to the guidelines of the European Society of Cardiology) [11], determined by being overweight (body mass index >25.1 kg/m^2^) and by the concomitant presence of at least one of the following criteria:Waist circumference >88 cm (women) or >102 cm (men)Circulating levels of total cholesterol >190 mg/dL, not on drug treatment (measured no more than 3 months prior to the start of the study)Circulating levels of LDL cholesterol >115 mg/dL, not on drug treatment (measured no more than 3 months prior to the start of the study)Circulating levels of triglycerides >150 mg/dL, not on drug treatment (measured no more than 3 months prior to the start of the study)Circulating levels of fasting blood glucose >110 mg/dL but <126 mg/dL, not on drug treatment (measured no more than 3 months prior to the start of the study)

*Exclusion criteria* are the presence of a current serious illness or unstable condition that requires physician supervision of diet or physical activity (e.g. recent myocardial infarction, chronic liver disease, inflammatory bowel diseases); pregnancy or intention to become pregnant in the next 18 months; lactation; current or recent (past 6 months) participation in weight loss treatment program or use of weight loss medication; no regular intake of meat, fish or poultry for the past month.

The study procedures are depicted in Fig. 1. There will be five clinical evaluations of the study population: one before the dietary intervention (*Time 0*), one 1.5 month after the start of the first dietary intervention (*Time 1*), one 3 months after the start of the first dietary intervention and at the time of intersection between the two groups (*Time 2*), one 4.5 months after the start of the study and 1.5 month from the intersection (*Time 3*), and the last one 6 months after the start of the study and 3 months from the intersection (*Time 4*). This design was chosen to ensure that there will be adequate time to achieve steady-state levels of lipid, glucometabolic, inflammatory and oxidative stress parameters.

**Fig. 1 Fig1:**
[figure not shown]
Organization of the intervention study

Compliance with the intervention is critical to the success of this project and will be achieved using behaviour change strategies including self-monitoring and regular phone calls for dietary counselling. Furthermore, a dietician will provide the participants with a detailed 1-week menu plan for each dietary period, with all food ingredients expressed in weight and/or volume measures, and a handout containing details on their assigned diet, including food groups that can be included and ones that should be avoided. The vegetarian menu plan will also include recipes for preparing meals. Sessions for the two groups are similar in duration and content, except with regard to dietary details, and group leaders will be instructed to make no comment favouring one diet over the other or indicating their own dietary habits.

Participants may discontinue the intervention or withdraw from the study for the following reasons: (1) at the request of the participant or (2) if the investigator considers that a participant’s health will be compromised due to adverse events or concomitant illnesses that develop after entering the study.

### Outcomes

#### Primary outcome

The primary outcome is total weight change from baseline.

#### Secondary outcomes

The secondary outcomes are:Fat mass change from baselineBody mass index (BMI) change from baselineLipid profile change from baseline (total cholesterol, LDL cholesterol, HDL cholesterol, triglycerides)Glycemic profile change from baseline (fasting glucose, insulin, HbA1c)Inflammatory parameters’ change from baseline [hs-CRP (high-sensitivity C-reactive protein), circulating levels of inflammatory cytokines: IL-1ra (interleukin-1ra), IL-1β (interleukin-1 beta), IL-2 (interleukin-2), IL-4 (interleukin-4), IL-6 (interleukin-6), IL-8 (interleukin-8), IL-10 (interleukin-10), IL-12 (interleukin-12), IL-17 (interleukin-17), IL-18 (interleukin-18), TNF-α (tumor necrosis factor alpha), IFN-γ (interferon gamma), VEGF (vascular endothelial growth factor), MCP-1 (monocyte chemoattractant protein-1), IP-10 (IFN-γ-inducible protein 10)]Oxidative stress markers’ change from baseline (total antioxidant profile, parameters of lipid peroxidation)

### Sample size

The sample size was determined on the basis of previous studies conducted to test the efficacy of a vegetarian diet on patients with type 2 diabetes mellitus [12]. To achieve an effect size between 1.25 and 2.1 for a power of 80 % at alpha < 0.05, for two groups, with a mean difference between groups from 2 to 3.5 kg and a standard deviation between 1.6 and 3.9, a sample size of at least 50 in each group of the study was required. It is projected that 100 subjects will be required in the final database and 10–25 % more must be randomized to achieve this number of completed subjects. These projections will be reviewed throughout the course of the study. Losses will be included in the intention-to-treat but not in the per-protocol analyses. The sample size calculation was performed using an online calculator software (available at http://www.powerandsamplesize.com).

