Sensitivity analyses will be undertaken, based on the assumption that missing outcomes are the worst possible, or the best possible, in different randomization groups. If these show that conclusions may differ based on missing values, then supplementary multiple imputation for missing values will be undertaken. These analyses will account for results of any losses to follow-up insofar as they pertain to differences in measured variables (i.e. under the assumption of missing at random).

For questionnaire items related to acceptability, differences between responses during the vegetarian and Mediterranean diet phases will be tested using the Wilcoxon matched-pairs signed ranks test. The independent samples Mann-Whitney U test will be used to compare the diet groups. To test for differences in reported benefits and adverse effects of the diets, the chi-square test for independent samples will compare the two diet groups regarding frequency of changes in reported symptoms from baseline to final time points, and paired-comparison *t* tests will assess within-group changes over time. A *P* value < 0.05 will be considered statistically significant.

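### The sample-size statement is internally inconsistent: its effect sizes need 12 and 5 per group, not 50, and the number to randomise differs between the Abstract and the Methods

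*Protocol article*

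**What the plan says.** The Sample size section of the protocol article puts the whole justification in one sentence. The target is given as "To achieve an effect size between 1.25 and 2.1", "for a power of 80 % at alpha < 0.05, for two groups". The inputs are given as ranges, "with a mean difference between groups from 2 to 3.5 kg and a standard deviation between 1.6 and 3.9", and the result is that "a sample size of at least 50 in each group of the study was required". Neither the sidedness of the test nor what the SD measures is stated: it could be the SD of body weight, of a change over one diet phase, or of a within-person difference.

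The same section then says "It is projected that 100 subjects will be required in the final database", and adds that 10 to 25 % more must be randomised to reach that number. The Abstract (Methods/design) says "A total of 100 subjects will be included and randomly assigned to two groups", with 50 in each.

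The Study design and setting section justifies the crossover by its smaller error variance, "reducing the sample size required to find a significant effect due to increased statistical power". The Statistical analysis section says that the data are paired and that both periods are used.

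**The concern.** An effect size is the difference divided by the SD, so the three stated ranges (effect size, difference, SD) must agree, and together with power and alpha they must lead to the stated number. An effect size of 1.25 is very large and needs only about a dozen people per group, so 50 cannot follow from it. If the 50 follows from something else, the article does not say what.

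This is the only justification given for the size of the trial on its primary outcome. As printed, a reader cannot tell what difference the trial was built to detect, or with what power, and so cannot judge how informative a null result would be. Two different randomisation totals also leave it unclear whether 100 is the number entering or the number completing. Enrolment was still under way when the article was submitted.

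**Working it through.** **Inputs.** From Sample size: difference 2 to 3.5 kg; SD 1.6 to 3.9 (kg assumed); effect size 1.25 to 2.1; power 80 %; alpha 0.05; two groups. From Recruitment and randomization: 1:1 allocation. Two-sided testing is taken as implied: the stated aim is a difference without direction, and the between-diet test includes a one-way analysis of variance.

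**Formula.** Effect size d = difference / SD. Number per group ≈ 2 × (1.96 + 0.842)² / d², then raised to the smallest whole number at which the exact (noncentral t) power reaches 80 %.

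**Step 1: the plan's own effect sizes.**
- d = 1.25: 2 × 7.85 / 1.5625 = 10.05; exact t, 12 per group.
- d = 2.1: 2 × 7.85 / 4.41 = 3.56; exact t, 5 per group.

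The stated 50 is not reproduced. With 50 per group, d = 1.25 would have more than 99.9 % power.

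**Step 2: the plan's own differences and SDs.**

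| Difference (kg) | SD | d | Normal approximation | Exact t, per group |
|---|---|---|---|---|
| 3.5 | 1.6 | 2.19 | 3.3 | 5 |
| 2 | 1.6 | 1.25 | 10.05 | 12 |
| 3.5 | 3.9 | 0.90 | 19.5 | 21 |
| 2 | 3.9 | 0.51 | 59.7 | 61 |

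The printed lower limit of 1.25 equals 2/1.6, and the upper limit of 2.1 is close to 3.5/1.6 = 2.19. The effect-size range therefore reflects SD 1.6 only. At SD 3.9 the largest possible effect size is 0.90, outside the printed range. No corner gives 50.

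**Step 3: what 50 per group does correspond to.** With 50 per group, 80 % power is reached at d = 0.566, or about 0.57. That is 2 kg at SD 2/0.566 = 3.53, or 3.9 × 0.566 = 2.21 kg at SD 3.9. Such pairs lie inside the stated ranges, but the article names none of them, and d = 0.57 is less than half the smallest effect size it prints. At 2 kg and SD 3.9, the exact two-sided two-group power with 50 per group is 72 %.

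**Step 4: other readings tried.**
- One-sided 0.05 at 2 kg and SD 3.9 gives 48 per group.
- Taking 1.6 and 3.9 as the SDs of the two arms gives a pooled SD of √((1.6² + 3.9²)/2) = 2.98, and 12 to 35 per group by the normal approximation.

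No reading tried reproduces effect size, difference, SD and number together.

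**Step 5: the crossover.** Assume that 3.9 is the SD of the weight change in one phase, equal in both phases, with no carryover. Let ρ be the correlation between a person's two phase changes. The documents give no ρ, so the range -0.5 to +0.5 is an assumption. The SD of the within-person difference is 3.9 × √(2(1 - ρ)). With 100 completers its standard error is one tenth of that (t test with 98 df, difference 2 kg).

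| ρ | SD of within-person difference | 2 kg / standard error | Power |
|---|---|---|---|
| -0.5 | 6.75 | 2.96 | 83 % |
| 0 | 5.52 | 3.63 | 95 % |
| +0.5 | 3.90 | 5.13 | 99.9 % |

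**Step 6: the totals.** Sample size: 100 completers, and 100 × 1.10 = 110 to 100 × 1.25 = 125 randomised. Abstract: 100 randomised, 50 + 50.

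**The case against.** The strongest reply is that the number is adequate even if the sentence is muddled. After the crossover every completer contributes to both diets, so 50 per sequence means 100 people per diet. A two-group formula is then conservative for any correlation above -1, given equal phase SDs and no carryover. That stands. A reader might infer from the 72 % that the trial misses its 80 % power. The documents do not support that, because 72 % belongs to a two-sided comparison of 50 against 50, whereas the Statistical analysis section brings in both periods as paired data.

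A second reply is that 50 lies within reach of the stated inputs. This also stands: it would be too strong to say that no stated input yields 50, since interior pairs such as 2 kg at SD 3.53 do. But those pairs are not named and contradict the printed effect sizes.

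A third is that 50 is a one-sided worst case (48) rounded up. Nothing in the article says one-sided, the aim has no direction, and d = 0.51 still falls outside 1.25 to 2.1.

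On the totals, the Abstract's 100 may be a loose summary of the completer target. A reader might infer that only 100 will enter and fewer will finish, but the Methods explicitly call for more to be randomised. The mismatch is one of wording, though it concerns the recruitment target and should be removed.

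The point does not depend on an unseen analysis plan or on condensation: the printed figures contradict each other.

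**Conclusion.** The sample-size statement is wrong as written and cannot be reproduced. Its effect sizes imply 12 and 5 per group, its differences and SDs imply 5 to 61, and 50 follows only from an unnamed pair with d about 0.57. The effect-size range leaves out SD 3.9. The calculation ignores the pairing on which the design is justified and does not define its SD. These results assume a two-sided test at 0.05 and exact t calculations; the one-sided reading does not remove the contradiction.

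The defect lies in the justification and is not evidence of inadequate size. The crossover power of about 83 % to 99.9 % at 2 kg rests on the assumptions in step 5, which the documents neither confirm nor rule out. The 100 versus 110 to 125 mismatch is a separate, smaller inconsistency. This should be fixed; it does not call the design or the number of patients into question.

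**What to change.** 1. Correct the effect-size range, and state the one difference, the one SD and what it is the SD of, the sidedness and the formula behind the 50. If these can no longer be recovered, state the property of the chosen size instead: in a two-sided two-group comparison, 50 per group detects d = 0.57 with 80 % power.
2. Give as the power of the design the figure for the paired crossover comparison with 100 completers, together with the assumed SD of the within-person difference. Label any two-group figure as such, so that 72 % is not read as the power of this trial.
3. Align the Abstract with the Sample size section: 100 completers, 110 to 125 randomised.

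The cost is one rewritten paragraph and one figure in the Abstract. Design and analysis stay as they are, and no patients are needed beyond those the Sample size section already foresees.

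### The sample-size figures contradict each other: effect sizes of 1.25 to 2.1 do not fit the stated SD range and would need about 5 to 12 per group, and the inputs behind 50 per group are not identified

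*Protocol article*

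**What the plan says.** All the inputs stand in one sentence of the Sample size section of the protocol article:

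- Effect size: "To achieve an effect size between 1.25 and 2.1".
- Power, alpha and structure: "for a power of 80 % at alpha < 0.05, for two groups".
- Difference: "with a mean difference between groups from 2 to 3.5 kg".
- Spread: "a standard deviation between 1.6 and 3.9", with no unit and no statement of whether it is a between-subject SD or the SD of within-person differences.
- Result, tied directly to these two ranges: "between groups from 2 to 3.5 kg and a standard deviation between 1.6 and 3.9, a sample size of at least 50" in each group.

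The section then plans for 100 completers and randomises 10 to 25 % more to reach that number, so 50 per group is already net of losses. It does not say which difference belongs with which SD, or whether alpha is one- or two-sided. The aim at the end of the Background is non-directional: the trial "will test whether there is a difference between a vegetarian calorie-restricted diet and a Mediterranean calorie-restricted diet".

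**The concern.** An effect size for a comparison of means is the difference divided by the SD. The sentence prints all three quantities, so they can be checked against one another and against the sample size. They fail both checks. The printed effect sizes do not cover the printed differences and SDs, and they call for a far smaller trial than the one described.

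This paragraph is the article's only justification of size for the primary outcome, weight change. As printed, a reader cannot tell whether the trial was sized for an effect of about 0.57 or for one more than twice as large. The section also says that the projections will be reviewed during the study, and such a review needs one definite target difference and SD.

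**Working it through.** **Inputs**, all from the Sample size section unless noted: difference 2 to 3.5 kg; SD 1.6 to 3.9; effect size 1.25 to 2.1; power 80 %; alpha 0.05; two groups; at least 50 per group. Allocation is 1:1 (Recruitment and randomization). Two-sided testing is inferred from the non-directional aim; one-sided results are shown beside it.

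**Step 1. Effect sizes from the stated differences and SDs**, d = difference / SD:

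| Difference (kg) | SD 1.6 | SD 3.9 |
|---|---|---|
| 2 | 1.25 | 0.51 |
| 3.5 | 2.19 | 0.90 |

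The inputs span 0.51 to 2.19. To reach d = 1.25 even with the largest difference, the SD can be at most 3.5 / 1.25 = 2.8. The printed range therefore excludes every SD above 2.8, although SDs up to 3.9 are printed in the same sentence. This step depends on neither sidedness nor the choice of test.

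**Step 2. Sample size for the printed effect sizes.** The normal approximation is n per group = 2(z_alpha + z_power)² / d². The squared sum is (1.960 + 0.842)² = 7.849 two-sided and (1.645 + 0.842)² = 6.183 one-sided.

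- d = 1.25, two-sided: 2 × 7.849 / 1.5625 = 10.05, so 11; the t test gives 12.
- d = 2.1, two-sided: 2 × 7.849 / 4.41 = 3.56, so 4; the t test gives 5.
- One-sided t test: 9 and 4.
- Two-sided t test at 90 % power: 15 and 6.

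None of these comes near 50. With 50 per group, power at d = 1.25 exceeds 99.9 %.

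**Step 3. Sample size at the corners of the stated differences and SDs** (80 % power, two-sided t test):

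| Difference / SD | d | n per group |
|---|---|---|
| 3.5 / 1.6 | 2.19 | 5 |
| 2 / 1.6 | 1.25 | 12 |
| 3.5 / 3.9 | 0.90 | 21 |
| 2 / 3.9 | 0.51 | 61 |

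For 2 kg with SD 3.9 the normal approximation gives 2 × 7.849 / 0.2630 = 59.7, so 60. With 50 per group, the power there is 71.9 % (t) or 72.7 % (normal). One-sided at 0.05, the same pair needs 48, and 50 per group gives 81.6 % (t).

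**Step 4. What 50 per group detects.** Solving the two-sided two-group t test for 80 % power at n = 50 gives d = 0.566. That corresponds to 2 kg if the SD is at most 2 / 0.566 = 3.53, or to 0.566 × 3.9 = 2.21 kg if the SD is 3.9. Both pairs lie inside the stated ranges, but the article names neither, and both contradict an effect size of 1.25 or more.

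**Step 5. Paired reading.** If 3.9 is the SD of within-person differences, 2 kg needs 7.849 × 3.9² / 2² = 29.8, so 30 participants in total (32 by t test), and 100 completers give 99.9 % power. If 3.9 is the SD under each diet and the within-person correlation is zero, the SD of differences is 3.9 × √2 = 5.52, and 100 completers give about 95 %. Neither version yields 50 per group.

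**The case against.** Four replies deserve a hearing.

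**One-sided testing.** The section does not state sidedness. One-sided at 0.05, 2 kg with SD 3.9 needs 48 per group, so at least 50 would be met even at the least favourable pair. This stands as a possibility, and a flat claim that 50 follows from none of the inputs would be too strong. It is not the likelier reading, because the aim is to test for a difference in either direction. It also does not rescue the effect sizes, since that pair has d = 0.51.

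**50 lies inside the span.** The stated differences and SDs call for anything from 5 to 61 per group two-sided, and pairs such as 2 kg with SD about 3.5 give 50. That is correct. The fault is not that 50 is unreachable but that no pair is named and the printed effect sizes fit none that would give it.

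**The crossover.** The Study design and setting section justifies the design by its smaller error variance, and the Statistical analysis section treats the data as paired. A reader might infer from 72 % that the trial is underpowered. The documents do not support that. The figure applies to a parallel, two-sided comparison, and with 100 completers a paired comparison at 2 kg and SD 3.9 has about 95 % power or more unless the within-person correlation is negative. The two-group reading of the calculation is still fair, because the section speaks of two groups and a number in each, and the analysis section also plans independent-sample t tests.

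**Origin of the range.** A reader might infer that both effect sizes were obtained from the smallest SD alone. The match is exact for 2 / 1.6 = 1.25, but 3.5 / 1.6 is 2.19, not 2.1, and other pairs also give 1.25 (2.5 / 2.0, for example). How the range arose is conjecture, and the contradiction does not depend on it.

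The dropout allowance explains nothing here, because it is added on top of the 100 completers. Nor is this a matter of condensed reporting: the figures are printed and disagree.

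**Conclusion.** The concern holds in this form: the sample-size sentence is internally inconsistent. Without any assumption about test or sidedness, the printed effect sizes exclude all SDs above 2.8, while SDs up to 3.9 are stated. At 80 % power those effect sizes need 5 to 12 per group two-sided, or 4 to 9 one-sided, against the stated 50.

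The shortfall at the pessimistic corner (61 per group needed, about 72 % power with 50) is conditional. It assumes a two-sided, two-group t test and that 3.9 is a between-subject SD. The aim and the wording of the section favour that reading, but the article does not state it. The figure describes the calculation as written and should not be taken as the power of the crossover comparison. Nothing here shows that the number of participants is too small.

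**What to change.** Keep the sample size and correct the paragraph:

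1. Delete the effect-size range of 1.25 to 2.1, or replace it with one that follows from the stated differences and SDs (0.51 to 2.19).
2. State the single difference, the SD and its type (between-subject, or of within-person differences), the sidedness and the test on which 50 per group rests.
3. Restate what 50 per group detects. If the basis is a two-sided two-group t test, suitable wording is: with 50 completers per group, the parallel-group comparison has 80 % power for an effect size of about 0.57 (2 kg if the SD is at most about 3.5 kg, or about 2.2 kg if the SD is 3.9 kg) and about 72 % power for 2 kg with SD 3.9 kg.
4. If the paired crossover contrast is the primary comparison, give its power separately, with the SD of within-person differences that it assumes.

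The cost is wording only. The stated parallel-group power at the pessimistic corner becomes less favourable: about 72 % in place of 80 %.
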